## Abstract

**Introduction:**

Cancer-related fatigue (CRF) is a common symptom of cancer and/or its treatment. Most cancer patients are affected during treatment, as well as years thereafter. Around a third of survivors report suffering from CRF. Those affected are often restricted in their everyday life. Acute and chronic stress are factors that increase a person’s vulnerability to develop CRF. In previous studies different instruments measuring acute and chronic stress related to CRF were used. However, a global instrument to determine individual stress load is lacking.

**Methods:**

Therefore, a developed global stress index (GSI) combining specific measuring instruments for acute and chronic stress is validated on an oncological sample and its influence on fatigue is examined. It is hypothesized that individuals with a high global stress load measured by the GSI report higher levels of CRF. The data will be collected using questionnaires in participants suffering from breast cancer with a curative treatment approach. Participants will be surveyed during tumor-specific therapy and six months later. They receive a consultation if fatigue symptoms are strongly pronounced. The study is registered at Deutsches Register Klinischer Studien, no. DRKS DRKS00027864.

**Discussion:**

This will be the first study using the GSI as a valid measure for surveying longitudinally acute and chronic stress load in an oncological sample in relation to CRF symptom development. The GSI may help to identify tumor patients with high levels of stress in good time and thus prevent chronic fatigue.

## Introduction

1

Fatigue is defined as a distressing and persistent feeling of physical, emotional or cognitive tiredness or exhaustion that is not related to recent activity and interferes with a person’s normal level of functioning (Fukuda, 1994; National Comprehensive Cancer Network, 2018). Symptoms of fatigue can be varied and range from feelings of lack of energy or exhaustion to depressive symptoms such as loss of drive or interest and difficulty concentrating. Those affected describe restrictions in their family and social life. These include difficulties in coping with everyday life, difficulties at work and a higher probability of unemployment, depressive and anxiety symptoms, lower quality of life and higher mortality rates (Sharpe et al., 1991; Curt et al., 2000; Scott et al., 2011; Weis, 2011; Horneber et al., 2012; Thong et al., 2020).

Fatigue is one of the most common side effects of cancer and cancer therapies (cancer-related fatigue—CRF). It occurs across various tumor entities as well as during or after therapy (Weis, 2011; Bower, 2019). During therapy, 50–90% of cancer patients are affected by CRF (Minton et al., 2013; Thong et al., 2020). In a recent meta-analysis, the average prevalence was 52% (Ma et al., 2020). In the long term—up to ten years after completion of therapy—around 30% of patients suffer from CRF (Kuhnt et al., 2011; Wu et al., 2019; Fabi et al., 2020). The high symptom burden, the effects on participation in everyday life described above and the reduced quality of life of those affected show the need for timely recognition of risk factors of developing CRF and specific treatment. The effectiveness of non-pharmacological forms of treatment, such as psychosocial (especially psychoeducation) and mindfulness-based (especially yoga) interventions or physical training, has already been proven and recommended (Bower, 2014; Fabi et al., 2020; Haussmann et al., 2022).

The risk factors that increase a person’s vulnerability to develop CRF include, in particular, psychosocial factors such as a history of depression, an anxious personality structure, loneliness, acute stress and traumatic childhood experiences (Lockefeer and De Vries, 2013; Bower et al., 2018; Bower, 2019). Women with breast cancer who perceive their tumor disease as a threat were also found to be associated with CRF (Levkovich et al., 2015). Numerous studies indicate that childhood experiences of abuse, maltreatment and neglect as well as cumulative stress over the lifespan are associated with CRF (Fagundes et al., 2012; Witek Janusek et al., 2013; Han et al., 2016; Bower, 2019). Women with breast cancer who had experienced trauma in childhood suffered significantly more frequently and more intensely from CRF than non-traumatized women with breast cancer. Similar associations were found for cumulative stress experience and CRF: women with breast cancer affected by CRF showed more acute and chronic stressors than women with breast cancer without CRF (Bower et al., 2014).

These previous studies have used different measurement instruments, e.g., traumatic childhood experiences were recorded with the Childhood Trauma Questionnaire (CTQ; Bernstein et al., 1994) and stress experienced during cancer with individual scales like the Perceived Stress Scale (PSS-10; Cohen et al., 1983). Since traumatic life events are part of the cumulative stress experience over the life span and symptoms such as depression and anxiety are also an expression of the cumulative stress load, it would be desirable to be able to define a global stress load measure across all the dimensions mentioned individually for a patient. In preliminary work by our working group (Maier et al., 2021), such a global stress index (GSI) using validated measurement scales in a sample of 192 healthy soldiers as part of a study funded by the Federal Ministry of Defense [Bundeswehreinsatz und Stress-Studie (BEST)] has been developed. For this purpose, validated measurement instruments of acute and chronic stress from childhood to adulthood were tested and converted into a GSI using structural equation modeling. Validation is currently underway in a healthy sample with an elevated cardiovascular risk profile.

### Aims of the prospective study

1.1

It is important to identify risk factors at an early stage and offer early treatment to the patients with high psychosocial stress load. Therefore, the present study examines whether the GSI can be validated in an oncological sample in order to develop a global stress measure for acute and chronic stress for tumor patients as well. It is assumed that the GSI is also suitable as a stress measure for oncology patients. Furthermore, it is investigated which effects cumulative stress experience has on CRF in women with breast cancer with a curative treatment approach. It is assumed that women with a higher GSI score report a higher level of CRF.

## Method and analysis

2

The study is being implemented as a monocentric, longitudinal study at the General Hospital Nuremberg, Paracelsus Medical University. To develop a GSI for oncological patients, women with breast cancer are asked about acute and chronic stressors and fatigue. For ethical reasons, a psychotherapeutic counselling session was offered in the presence of fatigue.

### Recruitment

2.1

In close cooperation with the Breast Center at the General Hospital Nuremberg *N* = 200 women will be recruited. All patients discussed in the tumor board conference who meet the inclusion criteria will be identified by the study staff and invited to participate in the study during their subsequent medical consultation. After verifying inclusion and exclusion criteria, patients are informed about the study’s purpose, potential benefits, and risks before signing the consent form. After agreeing to take part in the study (written consent), the women receive a set of questionnaires during tumor-specific therapy, about 8 weeks after being included into the study. If a clinically relevant problem (e.g., severe psychiatric illness, self-endangerment or endangerment of others) is identified during the recruitment, the patient will be offered a psychological treatment (inpatient or outpatient treatment in the Department of Psychosomatic Medicine and Psychotherapy or in the Department of Psychiatry and Psychotherapy).

### Inclusion and exclusion criteria

2.2

Inclusion criteria are a curative treatment approach (including chemotherapy and/or radiation and/or hormone therapy and/or immunotherapy) in women diagnosed with breast cancer. Exclusion criteria are palliative disease/treatment situation, severe psychiatric illness, untreated physical illness, malnutrition, cognitive impairment and insufficient knowledge of the German language.

### Patient survey

2.3

The GSI survey consists of the following questionnaires that will be carried out on the participants:

Perceived Stress Scale (PSS-4) (Cohen et al., 1983)Trier Inventory for Chronic Stress (TICS) (Schulz et al., 2004)Hospital Anxiety and Depression Scale (HADS) (Herrmann-Lingen et al., 1995)Childhood Trauma Questionnaire (CTQ) (Bader et al., 2009)Posttraumatic Diagnostic Scale Checklist (PDS) (Ehlers et al., 1996)The Deployment Risk and Resilience Inventory (DRRI-2) (Vogt et al., 2013)

The EORTC QLQ-FA12 (The European Organisation for Research and Treatment of Cancer Quality of Life Group, 2016) is used to record CRF. In addition, socio-demographic variables such as gender, age, education and marital status are surveyed. Completing the questionnaires will take about 45 min in total. Patients with high fatigue symptoms will receive a counselling session and, if necessary, further treatment.

### Data collection

2.4

The women receive the questionnaire by post. They answer it during the tumor-specific therapy (T1) and six months later (T2) (Figure 1). The women return the questionnaire in a prepaid envelope. If we detect fatigue after the evaluation, we contact the women for a consultation for ethical reasons.

**Figure 1 fig1:**

Study procedure and consultations.

### Consultation

2.5

If fatigue is less pronounced, the women receive written information on fatigue and its treatment options. If patients with high fatigue symptoms are identified, they receive a counselling session by the psychosomatic consultation liaison services and, if necessary, further treatment. The counselling session takes place by telephone or in the clinic. After a detailed medical history, which includes questions about the status of tumor-specific therapy, physical and mental illnesses, the Cella et al. (1998, 2001) criteria are used to confirm the presence of CRF. The recommendations to patients are based on the guidelines that refer to CRF (Fabi et al., 2020; Howell et al., 2015). In addition to physical exercise, mindfulness-based and psychotherapeutic treatment approaches are recommended and patients are referred for further inpatient or outpatient treatment.

### Data analysis

2.6

The sample size of *N* = 200 will be calculated over the A-priori Sample Size Calculator for Structural Equation Models^1^ analogous to the validation study of the GSI by Maier et al. (2021).

Data are evaluated in anonymized form. The women are given a pseudonym to complete the questionnaires. As the DRRI-2 with the reformulated item has not yet been examined for psychometric properties, construct validity will be evaluated using confirmatory factor analysis, and internal consistency will be assessed through reliability analyses (Cronbach’s *α*). Subsequently, the GSI is tested using the open-source software R (R Core Team, 2017). Item distribution and the variance between the items are considered first. The multivariate normal distribution in the whole item set is examined. In Maier’s study (Maier et al., 2021), the stress index was tested on a healthy sample using an iterative procedure at item level. Various models were tested. Finally, a hierarchical multilevel model with a g-factor was selected. The g-factor was the highest order to which the latent variables (perceived stress, HADS and CTQ) load directly. At a third level are the subscales of the CTQ, which have an additional informative influence on the GSI. The manifest variables (DRRI-2 and PDS) are at the lowest hierarchical level. In the present study, this proposed method is now to be reviewed and tested to see whether the factor structure is also evident in the oncological sample. It is also investigated whether the combination of all scales provides an additional value.

Correlations between the GSI and CRF are calculated using Pearson correlations. Predictions of GSI on fatigue are determined using regression models. The course of the fatigue symptoms is calculated with pre-post comparisons either using parametric or non-parametric tests depending on the distribution of the collected data.

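### The GSI contains HADS while the article counts depressive symptoms within fatigue, so a GSI–fatigue association is partly built in and cannot by itself show an effect of cumulative stress

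*Protocol article*

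**What the plan says.** **Question.** Under Aims of the prospective study, "it is investigated which effects cumulative stress experience has on CRF in women with breast cancer". The working hypothesis there is that a higher GSI score goes with more CRF.

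**Predictor.** Patient survey opens its list with "The GSI survey consists of the following questionnaires that will be carried out on the participants", and names PSS-4, TICS, HADS, CTQ, PDS and DRRI-2. Data analysis describes the model to be re-tested: "The g-factor was the highest order to which the latent variables (perceived stress, HADS and CTQ) load directly". HADS is included on purpose, because the Introduction holds that "symptoms such as depression and anxiety are also an expression of the cumulative stress load".

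**Outcome.** CRF is recorded with the EORTC QLQ-FA12. The Introduction describes fatigue symptoms as running from lack of energy or "exhaustion to depressive symptoms such as loss of drive or interest and difficulty concentrating". A later sentence lists "depressive and anxiety symptoms, lower quality of life and higher mortality rates" among the restrictions that affected people describe.

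**Analysis.** "Correlations between the GSI and CRF are calculated using Pearson correlations", followed by regression models for predicting fatigue from the GSI. The nearest related statement is "It is also investigated whether the combination of all scales provides an additional value". It comes directly after the factor-structure test and names neither a comparator nor a criterion.

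**The concern.** The article places depressive symptoms on both sides of the association: inside the index that is to explain fatigue, and inside the range of symptoms that make up fatigue. HADS, perceived stress and FA12 are also completed in the same questionnaire set, the first time during tumour therapy. Current fatigue can therefore raise current distress scores as well as the reverse.

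The planned analyses use the whole GSI. A positive result would fit two accounts: that cumulative stress goes with more fatigue, or that women who are fatigued now also score high on a depression and anxiety scale now. The second aim is worded as an effect of cumulative stress experience, and the Discussion goes on to early identification of patients at risk. If the whole-GSI result is the only evidence, the study cannot say which account it supports, nor whether the index does more than HADS alone.

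**Working it through.** The article gives no figure for this association to reproduce. N = 200 cannot be re-derived either, because the inputs to the sample-size calculator are not stated. The check asks what GSI–FA12 correlation would arise if fatigue correlated with HADS and with no other GSI component.

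**From the article:** N = 200; three factors loading directly on the g-factor (perceived stress, HADS, CTQ).

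**Assumed:** equal weights on standardised parts; intercorrelations 0.70 (perceived stress–HADS), 0.25 (perceived stress–CTQ) and 0.30 (HADS–CTQ); HADS–FA12 from 0.3 to 0.6; two-sided 5% level.

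**Step 1, composite.** Variance of the sum = 3 + 2 × (0.70 + 0.25 + 0.30) = 5.5, and √5.5 = 2.345. The composite correlation is the sum of the part–FA12 correlations divided by 2.345.

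**Step 2, power.** By Fisher's z, power ≈ Φ(atanh(r) × √197 − 1.96), with √197 = 14.04. The smallest significant |r| is about 0.139.

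| HADS–FA12 (other parts 0) | GSI–FA12 r | atanh(r) × √197 | Power |
|---|---|---|---|
| 0.3 | 0.3/2.345 = 0.13 | 1.81 | 44% |
| 0.4 | 0.4/2.345 = 0.17 | 2.42 | 68% |
| 0.5 | 0.5/2.345 = 0.21 | 3.04 | 86% |
| 0.6 | 0.6/2.345 = 0.26 | 3.67 | 96% |

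**Step 3, dependence on the HADS weight** (HADS-only link throughout).
- Three equal parts, common intercorrelation ρ from 0.2 to 0.5, r = r_HADS/√(3 + 6ρ): a HADS link of 0.3 gives r 0.12 to 0.15 and power 41% to 54%. A link of 0.6 gives power 94% to 99%.
- g-factor regression score, assumed loadings 0.8/0.9/0.3 (perceived stress/HADS/CTQ): a link of 0.3 gives r 0.21 and power 86%. A link of 0.5 gives r 0.36 and power above 99%.
- g-factor score, loadings 0.7 each: a link of 0.5 gives r 0.21 and power 83%.
- Six equal parts, r = r_HADS/√(6 + 30ρ): a link of 0.5 gives r 0.11 to 0.14 and power 34% to 53%. A link of 0.3 gives power 15% to 23%.

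**Step 4, perceived stress also linked to fatigue, CTQ still unrelated** (weights of Step 1). With 0.30 for both HADS and perceived stress, r = 0.60/2.345 = 0.26 and power is 96%. With HADS 0.40 and perceived stress 0.30, r = 0.70/2.345 = 0.30. With 0.60 and 0.50, r = 1.10/2.345 = 0.47. Power in the last two cases is about 99% or more.

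**Step 5, HADS removed.** In the HADS-only case the remaining score has r = 0 and is significant 5% of the time. If perceived stress has its own link of 0.30, the score without HADS has r = 0.30/√(2 + 2 × 0.25) = 0.30/1.581 = 0.19. A GSI without HADS thus removes the depressive-symptom overlap but still carries current stress, so the pre-illness scales need a separate look.

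**The case against.** **The inclusion is deliberate and the literal hypothesis is testable.** The GSI is meant to cover acute and chronic stress, and the article gives its reason for counting depression and anxiety as an expression of stress load. This stands. It justifies building the index and testing whether a higher GSI goes with more CRF. It does not justify reading that association as an effect of cumulative stress when the outcome shares content with the index.

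**Regression may be prospective.** T1 GSI could predict T2 fatigue, and screening does not require separating causes. The article does not say which time points are used, and a lag would not remove shared content. For a pure screening claim the objection has force; for the wording of the aim it does not.

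**Overlap at item level is not shown.** Correct. The article describes fatigue in general and gives no FA12 or HADS items. The built-in part rests on its description of fatigue, and its size is unknown.

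**The added-value sentence and the full protocol may cover this.** The sentence could hold a comparison with HADS, but as written it has no comparator and is not tied to fatigue. A condensed article may leave such detail elsewhere, which is one reason for the modest grading.

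**Stronger readings that a reader might infer.**
- *That anxiety, too, is listed as a fatigue symptom.* It is not. The symptom sentence names depressive symptoms; anxiety appears among the associated restrictions.
- *That the hypothesis cannot fail.* The HADS-only power range starts at 44% with the Step 1 weights, and is lower with six parts.
- *That 0.30 to 0.47 measures the overlap.* That range includes perceived stress, which is intended stress content. The scenario is also artificial: zero CTQ–FA12 correlation alongside positive CTQ correlations with the other parts implies a negative partial coefficient for CTQ (−0.13 to −0.21), contrary to the direction of the studies that the article cites. The HADS-only case is artificial in the same way. Both are illustrations, not forecasts.

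**Conclusion.** The point holds in a limited form. By the article's own description, predictor and outcome share depressive-symptom content. A significant correlation or regression of CRF on the total GSI could well arise at N = 200 without any relation between the life-span components and fatigue. Under an equally weighted three-part composite with a HADS-only link of 0.3 to 0.6, r is about 0.13 to 0.26 and power about 44% to 96%. Both are higher if perceived stress also correlates with fatigue or HADS carries more weight, and lower if HADS is one of six equal parts. Every correlation, loading and weight here is an assumption, as is the 5% level; only N = 200 and the three top-level factors come from the article.

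The whole-GSI result therefore cannot by itself be read as the effect of cumulative stress experience on CRF. A reader might go further and hold that no stress effect may be claimed unless the pre-illness scales alone predict fatigue. The article does not support that, because its index is meant to include acute stress. The scales are collected separately, so nothing is lost irretrievably. This is a cheap improvement, not a must-fix.

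**What to change.** In section 2.6, keep the full-GSI correlation and regression, and pre-specify beside them:

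1. FA12 on a GSI score computed without HADS.
2. FA12 on the components that refer to the time before illness: CTQ, and DRRI-2 with its adapted introduction. Show PDS separately, because its reference period is not stated.
3. The GSI against HADS alone in explaining FA12, for example by cross-validated R², as the criterion for added value with respect to fatigue.

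Add a rule for wording: if the association disappears without HADS, describe it as an association with current distress, not as an effect of cumulative stress. Do not make every claim conditional on item 2.

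The cost is two or three extra regressions on data already collected and a short addition to section 2.6. The downside is that the headline association may look weaker. The additions should be fixed before the data are analysed, since choosing them afterwards would be less credible.

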## Discussion

3

To the best of our knowledge, this will be the first study to combine instruments of acute and chronic stress and transfer them into a Global Stress Index (GSI) in an oncological sample. Study patients receive the questionnaire set during oncological therapy and 6 months later, measuring acute and chronic stress as well as CRF. Women suffering from severe fatigue symptoms will receive a psychological counselling session and, if necessary, further treatment.

In the following studies investigating stress and CRF, several individual measurement instruments were used: Han and colleagues (Han et al., 2016) examined breast cancer patients in a prospective longitudinal study during and 6 weeks after radiotherapy and showed that women who had experienced childhood trauma (CTQ; Bernstein et al., 1994) suffered significantly more from CRF than women who had not experienced childhood trauma before. The traumatized women also reported higher levels of depression (Inventory of Depressive Symptomatology-Self Reported (IDS-SR); Rush et al., 1996) and acute stress (PSS-10; Cohen et al., 1983). Witek Janusek et al. (2013) showed that childhood trauma (CTQ; Bernstein et al., 1994) increased vulnerability to fatigue, perceived stress (PSS-10; Cohen et al., 1983) and depressive symptoms (CES-D; Radloff, 1997), lower quality of life and immunological dysregulation in breast cancer patients. Women who were neglected or abused (CTQ; Bernstein et al., 1994) as children reported more cancer-related psychological stress [Impact of Events Scale (IES); Horowitz et al., 1979], more fatigue and a lower sense of well-being after tumor treatment (Fagundes et al., 2012). Breast cancer patients who completed their treatment and suffered from persistent fatigue showed a higher cumulative stress experience (STRAIN; Slavich and Epel, 2010), including childhood traumatization (CTQ; Bernstein et al., 1994), compared to patients who did not suffer from fatigue (Bower et al., 2014). The present study will combine these individual measurement instruments (GSI) which can be used as a screening instrument in clinical practice.

The DRRI-2 (Vogt et al., 2013) questionnaire is an instrument developed specifically for use with veterans. Section A is used in the GSI, which refers to life events prior to deployment. For the oncology sample, we rephrased the introduction “before my deployment” to “before my illness.” In addition, item 15 was also adapted and generally refers to difficult professional situations. However, due to time constraints, it was not possible to validate the questionnaire with the reformulated item.

Although our sample only refers to breast cancer patients and the significance for other tumor entities may be limited, all patients treated at the breast center are addressed and asked for their participation in the study. Therefore, this is a representative sample of breast cancer patients. An expansion to other tumor entities may be possible in the future.

Our longitudinal study design makes it possible to observe the progression of CRF. This gives women at the Breast Center the opportunity to undergo CRF screening over 6 months. This is the first and only opportunity at General Hospital Nuremberg to screen for CRF as the guidelines recommend (Fabi et al., 2020; Howell et al., 2015). The women may benefit from a subsequent consultation and fatigue can be improved, which future results may show.

The use of the GSI in clinical practice can define the stress risk profile of an oncological patient individually and can help identifying potential risk factors for CRF at an early stage so that treatment may be successfully addressed.
